### Demographics

Date of birth, sex, weight (Kg), height (m) and medication will be recorded. Clinical characteristics of both parents will be directly examined and the genealogy of 3 consecutive generations will be drawn. The growth curves and medical history and medication use will be registered.

### Outcome measures

The outcome measures are listed in Table 1 and are structured according to the format of the International Classification of Functioning, Disability and Health for children and youth (ICF-CY [36]). The ICF is the World Health Organization framework for measuring health and disability at both individual and population levels and is subdivided in body functions, body structures, activities and participation and environmental factors. All procedures will be assessed at baseline visit and after 2-year follow-up if not otherwise specified.

**Table 1 Tab1:** Outcome measures and tests at baseline and follow-up

Outcome domain	Tests	Age
Primary outcome measure		
ICF: Activities and participation		
Motor function	Motor Function Measure [37, 38]	2–18
Secondary outcome measures		
ICF: body functions		
Mental functions	Education level (school level)	5–18
	EEG [48]^a^	0–18
	Denver II developmental screening test [49]	0–6
Seeing functions	Visual acuity (Snellen)	4–18
Hearing functions	Tone- and speech audiometry	2–18
Pain	Faces scale pain [50]	6–18
Cardiac function	ECG [51]	0–18
Aerobic exercise tolerance	6-minute walk test MWT [52, 53]	walk
Fatigability	NeuroQol fatigue domain [54]	2–18
Respiratory function	Forced vital capacity and forced expiratory volume Spirometry [55]	6–18
Digestive, defecation, weight maintenance and urination functions	Qualitative history	0–18
Ingestion functions	TOMASS-C test [56]	6–18
	Neuromuscular disease swallowing status scale [57]	2–18
	Dysphagia questionnaire [40, 58]	2–18
Muscle functions	Handgrip dynamometer	6–18
	Manual muscle testing [59]	0–18
	Serum creatine kinase (CK)	0–18
	Age-adjusted clinical severity scale [60, 61]	5–18
	FSHD evaluation score [62]	
ICF: Body structure		
Eye structure	Slit lamp examination	4–18
	Dilated fundoscopy	4–18
	Optical coherence angiography tomography	6–18
Movement related structures	Muscle ultrasonography [39]	0–18
	Spine x-ray^a^	4–18
ICF: Activities and participation		
Communication/social interactions	Social Economic Questionnaire SEV [63]^a^	4–18
Self-care/life areas	Kidscreen [64]	8–18
ICF: Environmental factors		
Products and natural environment	Qualitative anamnesis and history	0–18

^a^ Only if clinically indicated

Outcome measures are listed in Table 1 and are extensive due to the explorative character of the study. The primary outcome is the motor function as measured by the Motor Function Measure [37, 38]. This measure specifically includes axial and upper limb functions, is designed for both ambulatory and non-ambulatory patients and can be continued into adulthood. Motor performance is supplementary assessed using the 6 min walking test, handgrip dynamometer and manual muscle testing MRC-scores. The FSHD evaluation score and the age-adjusted clinical severity scale are scored to explore the validity of these scales in children. In addition, non-muscular symptoms are extensively tested based on earlier literature on childhood onset FSHD [9–11, 17–19].

Quantitative muscle ultrasonography (QMUS) will be used to screen for muscle myopathy/inflammation. QMUS is a patient-friendly non-invasive method to screen for dystrophic changes in skeletal muscle [39]. The technique has been well-validated for screening and follow-up in several childhood and adult neuromuscular disorders [40]. The following muscles will be measured on both sides, using a fixed scanning protocol and settings as previously described [41, 42]: depressor anguli oris, masseter, sternocleidomastoideus, biceps brachii, rectus abdominis, rectus femoris, gastrocnemicus and tibialis anterior [43, 44].

Extramuscular symptoms will be assessed based on symptoms as reported in literature. This will include an extensive ophthalmologic screening, including optical coherence tomography with angiography for specific focus on the retinal arteries [45], a tone- and speech audiometry, electrocardiogram (ECG) and spirometry. Electro-encephalography (EEG) and spinal x-ray will be performed if indicated.

#### Prevalence

An improvement of the prevalence estimations will be assessed by comparing our recruitment with anonymous data of the genetic testing by the Leiden University Medical Center, where all Dutch samples are tested. This method is based on earlier research in the adult population [4].

#### (Epi)genetic disease-modifying factors

To explore the relationship between (epi)genetic disease-modifying factors and the disease severity, an extensive qualitative history is taken. Focus is on medical history (traumata, infections), dietary intake and maternal and perinatal health, including maternal substance use.

From participants and biological parents (if available) high molecular weight DNA and RNA will be isolated from peripheral blood mononucleated cell (PBMCs). The sizing of the D4Z4 repeats on chromosomes 4 and 10 will be executed using pulsed field gel electrophoresis (PFGE) and the haplotype analysis by hybridization of PFGE blots with probes A and B in combination with PCR-based SSLP analysis [21, 22]. Methylation of the D4Z4 repeat will be established at the FseI restriction site in the proximal unit of the D4Z4 array [26, 27]. In case of reduced CpG methylation at D4Z4, gene mutations in SMCHD1 or DNMT3B will be analysed by Sanger sequencing and predicted splice site mutations or nonsense mutations will be further analysed using cDNA isolated from PBMCs.

For RNA isolation from PBMCs we use PAXgene Blood RNA tubes which will be processed for obtaining high quality RNA for whole genome RNA sequencing analysis (RNAseq).

#### Cohort for future trial acquisition

An additional goal of this study is to obtain a well-documented cohort for longer (>2 years) follow-up and future trial acquisition. Patients will be asked to participate in the Dutch FSHD registration study [46] and for biomaterial storage. Serum samples of the participant and both biological parents will be stored in the Radboud biobank (http://www.radboudbiobank.nl/nl/) and are available for future DNA and/or RNA research for researchers worldwide.

### Data collection

All parents/legal guardians of participants will receive an online form with the standardized questionnaires. All participants > 8 years will also receive an online form with the standardized questionnaires for children. The forms will be sent through Castor and directly stored in the Castor database (Version 2015, [47]). All data-management and data-monitoring will be performed within the Castor software.

### Statistics

The Statistical Package for the Social Sciences (SPSS version 22, IBM, Armonk, New York) will be used to conduct all statistical analyses. Due to the explorative nature of the iFocus study, descriptive statistics will be applied to describe all patient characteristics. Continuous data are described as mean ± standard deviations. If reference values are available from literature, we will check for overlapping confidence intervals. Number of non-missing values is described (missing data are not replaced) unless stated otherwise. For describing the D4Z4 CpG methylation corrected repeat size, the delta 1 score will be used [14].

Correlations between (novel) molecular markers and clinical severity will be assessed with Spearman rank correlation. Possible correlations will be assessed on the following variables: ‘corrected repeat length’, ‘age at investigation’, ‘hereditary pattern’ ‘age at onset’, various extramuscular symptoms, FSHD severity score and motor function measurement scores. If novel (molecular) variables are found, these will be added in the statistical model. To minimize the multicolinearity manual backward reduction will be executed.

For the clinical prediction model, multiple linear regressions will be used to explore the relationship between potential disease modifying variables and disease severity. In addition, for the 2 year follow-up data, linear mixed models will be applied for analysis of differences in disease progression. The primary outcome is a continuous variable, FSHD clinical severity score. The fixed effect predictors are repeat length (divided in 1–3 D4Z4 repeat units (U), 4–6 U and 7–10 U), current age, hereditary pattern and sex.

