### Study population

Eligible patients are children aged 0–17 years with symptoms of facioscapulohumeral dystrophy and genetically proven FSHD1 or FSHD2 living in The Netherlands. Exclusion criteria are: inability or unwillingness to provide informed consent. The aim is to include all children in The Netherlands with a genetically confirmed diagnosis of FSHD. We expect to include 20–30 patients based on the estimated prevalence in the population [4].

There is no agreement on the classification of children with FSHD. Therefore we chose to include all patients less than 18 years with genetically confirmed FSHD, including for example children with isolated hearing loss as well. This enables us to describe the complete spectrum of children with FSHD. In addition, this study could identify predictors of severity and prognosis, thereby serving as a reference for working towards a widely accepted classification.

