## Discussion

Results from the iFocus study will provide insights into the clinical and genetic spectrum of children with FSHD. These insights are vital for adequate symptomatic management and clinical trial-readiness. We propose extensive qualitative and quantitative measurements specified by age and use a modified format of the International Classification of Functioning, Disability and Health criteria. This structured approach enables us to give an explorative, full-spectrum, unbiased clinical description of FSHD in children.

Furthermore, this study aims to provide additional insight in the epigenetic and environmental disease modifying factors. This could help to unravel the aetiology of FSHD and serve as a basis for prognostic and therapeutic models.

One of the study’s strengths is the excellent recruitment organisation in The Netherlands, thereby reducing selection bias. There is a well-organized health system with free access to paediatric neurology for every child. In addition, our centers have a longstanding history of excellent FSHD research and administration. Finally, all participants can reach the study center within three hours. These assets make it possible to execute a population based, nation-wide study.

A critical issue is the small number of participants, making it hard to verify correlations or differences in subgroups, international collaborations are in preparation. Although, we expect to find differences in motor functioning after 2 years of follow-up, this period will possibly be too short for changes in other outcome measures such as wheelchair dependency. Therefore we aim to continue the follow-up of this cohort for a longer period of time.

In conclusion, the iFocus study is expected to yield new knowledge on children with FSHD, aiming to optimize clinical management, help unravelling the aetiology of FSHD and serve as a basis for prognostic and therapeutic studies.

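### Checking whether confidence intervals overlap is an over-conservative way to compare the cohort with reference values; an estimated difference with its own interval should replace it

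*Protocol article*

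**What the plan says.** The Statistics section of the protocol article sets the frame: "Due to the explorative nature of the iFocus study, descriptive statistics will be applied to describe all patient characteristics". It then gives the summary measure, "Continuous data are described as mean ± standard deviations", and the comparison with norms: "If reference values are available from literature, we will check for overlapping confidence intervals".

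The section gives no confidence level, decision rule or reference sample size for this comparison. It names no estimate of the difference, no one-sample test and no standardised score. It does not say what will be concluded when intervals overlap.

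Under Study population the article expects 20 to 30 children, aged 0–17 years. That number comes from prevalence, not from a power calculation. Table 1 gives an age range or a walking requirement for nearly every test, and the Discussion describes the approach thus: "We propose extensive qualitative and quantitative measurements specified by age".

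**The concern.** Checking for overlap is a familiar shortcut, but it does not ask whether two means differ. It adds the two half-widths, whereas the uncertainty of a difference combines the standard errors as a root sum of squares. The sum is the larger whenever both standard errors are above zero, so the check demands a bigger gap than a direct comparison would.

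This is a stated choice of method, not a detail left to a fuller document. It matters because comparison with norms is a natural way to judge whether children with FSHD fall short on measures such as spirometry, grip strength, walking distance or quality of life. With 20 to 30 children there is little precision to spare. An exploratory study also has much to lose from signals that are present but not noticed.

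**Working it through.** The plan states no alpha, power, effect size or reference sample size for this comparison, so there is no figure of its own to reproduce. What can be worked out is how the overlap check behaves.

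**Inputs.** From the document: 20 to 30 children (Study population); 25 is taken as the middle. Assumed, because the document is silent: 95% intervals, normal data, equal SDs in cohort and reference, and a reference sample from 25 up to a norm with negligible error. The 5% and 80% benchmarks are conventional yardsticks, not the plan's.

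**Formulas.** Let s1 and s2 be the standard errors of the cohort mean and the reference mean.

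- A direct comparison flags a difference when |difference| > 1.96 × √(s1² + s2²).
- The intervals fail to overlap when |difference| > 1.96 × (s1 + s2).
- On the scale of the direct test, the overlap check has critical value c = 1.96 × (s1 + s2) / √(s1² + s2²).
- Its real two-sided alpha is 2 × (1 − Φ(c)).
- A direct comparison has 80% power at a standardised shift of 1.960 + 0.842 = 2.802. At that shift the overlap check has power Φ(2.802 − c).

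**Example, 25 children against a reference of 100 (SD = 1).** s1 = 1/√25 = 0.200 and s2 = 1/√100 = 0.100. Then c = 1.96 × 0.300 / √0.050 = 1.96 × 1.342 = 2.63. Alpha is 0.0085. Power is Φ(2.802 − 2.63) = Φ(0.17) = 57%.

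**Results for 25 children**

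| Reference n | c | Real alpha | Power of overlap check where direct comparison has 80% |
|---|---|---|---|
| 25 | 2.77 | 0.0056 | 51% |
| 100 | 2.63 | 0.0085 | 57% |
| 200 | 2.50 | 0.012 | 62% |
| 300 | 2.43 | 0.015 | 65% |
| 1000 | 2.24 | 0.025 | 71% |
| fixed norm | 1.96 | 0.05 | 80% |

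The exact cohort size matters little. At a reference n of 100, power is 58%, 57% and 56% for 20, 25 and 30 children. The ratio of the two standard errors drives the result, and equal standard errors are the worst case.

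**Check by simulation.** With 100,000 runs per case, t-based 95% intervals and the Welch test as the direct comparison, the share of runs flagging the true difference was:

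- 25 against 25: 47% by non-overlap, 78% by Welch (with no true difference: 0.006 and 0.050)
- 25 against 100: 53% and 78%
- 25 against 1000: 68% and 77%

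The pattern is the same, with slightly lower power because the SDs are estimated.

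**Direction of the error.** Because s1 + s2 is never smaller than √(s1² + s2²), non-overlap always implies a difference at the 5% level. The check raises no extra false alarms; its only fault is that it misses differences.

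**The case against.** The strongest reply is that this is a descriptive check in a study that calls itself exploratory. No alpha or decision rule is attached to it, and the regressions, rank correlations and mixed models do not use it. Type I error is not inflated. If the published norm rests on a very large sample, the loss is small, and against a fixed norm it is nil: asking whether the cohort interval covers the norm is then the same as a one-sample test. All of this stands, and it limits the size of the point. It does not rescue the method, because an estimated difference with its interval is just as descriptive and tells the reader more.

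Three stronger readings are tempting, and the article does not support them.

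- A reader might call the check invalid. It is insensitive, not invalid: when it flags a difference, that finding is sound at the 5% level.
- A reader might infer that overlap will be reported as normality. The article never says so; the risk arises only if overlap is read that way.
- A reader might infer that raw values will be pooled over ages 0–17 and set against norms that cannot match. Pooling is not stated, and mean and SD can equally summarise z-scores. Table 1 starts spirometry and handgrip at 6 years and the Motor Function Measure at 2, and limits the walk test to children who walk. No reference sets are shown, so nothing can be said about whether they match. Leaving the handling of age to a fuller document is ordinary for an article.

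**Conclusion.** The point holds as a poor choice of method with a limited effect. The only comparison with reference values that the article names is over-conservative, and overlap under it is uninformative. For about 25 children its real alpha lies between 0.0056 and 0.05, and its power between 51% and 80% where a direct comparison has 80%. Where the truth falls in that range depends on reference sample sizes that the documents do not give. The figures rest on 95% intervals, equal SDs and approximately normal data.

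The loss is substantial for reference samples in the low hundreds or smaller and modest at 1000. Age standardisation belongs to the better method; its absence from this article is not a separate error. The change is worth making, but the study's other analyses do not depend on it.

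**What to change.** Delete the overlap check and state instead that each comparison with a norm will report the estimated difference from the reference with its own 95% confidence interval:

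- Where age- and sex-specific norms exist, convert each child's value to a z-score or percent predicted (using height where the norm requires it). Report the mean with its 95% interval as a one-sample comparison, against 0 for z-scores or 100 for percent predicted.
- Where only a reference mean, SD and sample size are published, report the difference in means with a Welch interval, restricted to the children in the matching age band.
- State that overlapping intervals will not be read as absence of a difference.

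Date of birth, sex, height and weight are already recorded (Demographics), so no new data are needed. The cost is a sentence or two in the plan and a little more routine analysis.

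### The statistics section calls the FSHD clinical severity score the primary outcome, so the declared primary, the Motor Function Measure, is the outcome of no stated longitudinal model

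*Protocol article*

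**What the plan says.** Under Outcome measures the protocol article states: "The primary outcome is the motor function as measured by the Motor Function Measure". The Methods/design part of the abstract says the same, and Table 1 lists the MFM alone under its primary outcome heading, for ages 2–18.

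The Statistics section then says that "for the 2 year follow-up data, linear mixed models will be applied for analysis of differences in disease progression". The next sentence is "The primary outcome is a continuous variable, FSHD clinical severity score", and the one after it lists the fixed effects: repeat-length group, current age, hereditary pattern and sex.

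Elsewhere in that section, the Spearman correlation list ends with "FSHD severity score and motor function measurement scores", and a general statement says that "descriptive statistics will be applied to describe all patient characteristics". The multiple linear regression for the prediction model takes disease severity as its outcome and names no instrument.

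Table 1 has no entry called FSHD clinical severity score. The two near matches are the age-adjusted clinical severity scale (ages 5–18) and the FSHD evaluation score (no age range given). Both are among the secondary outcomes, under muscle functions. The text under Outcome measures says that both "are scored to explore the validity of these scales in children".

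**The concern.** One article gives the label of primary outcome to two different instruments, and the one that receives the longitudinal model is not the one declared in the abstract, in Table 1 and in the outcome text. Someone writing the analysis code from the Statistics section would fit the 2-year mixed model to the severity score and would find no instruction to model the MFM over time.

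Three things are at stake. First, 2-year progression is a stated secondary objective, and the Discussion expects the change to show in motor functioning, yet no stated model has motor function as its outcome. Second, the score that is modelled is not clearly identified, and both candidates are scales whose validity in children the study itself sets out to explore. Third, with two outcomes carrying the same label, a reader of the results could not tell from the article which was meant to lead.

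**Working it through.** The point rests on comparing text. The article gives no power calculation, error rate or effect size for either outcome, so there is no planned figure to reproduce.

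**1. Which outcome is called primary, and where**

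| Place in the article | Primary outcome named |
|---|---|
| Abstract, Methods/design | MFM |
| Outcome measures, Table 1 | MFM |
| Outcome measures, text | MFM |
| Statistics | FSHD clinical severity score |

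Three places name the MFM and one names the severity score.

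**2. Which outcome each stated analysis uses**

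| Analysis in the Statistics section | MFM | Severity score |
|---|---|---|
| Descriptive statistics | covered by the general statement | covered by the general statement |
| Spearman correlations | listed | listed, as FSHD severity score |
| Multiple linear regression | not named (outcome is disease severity) | not named (outcome is disease severity) |
| Linear mixed models, 2-year data | not named | the only outcome named |

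Stated longitudinal models with the MFM as dependent variable: 0. With the severity score: 1.

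**3. Whether MFM data would exist for such a model.** Under Outcome measures, procedures are done at baseline and at 2 years unless stated otherwise, and nothing exempts the MFM. The data for an MFM model are therefore already planned.

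**4. Which instrument is modelled.** The name used in the Statistics section agrees exactly with neither Table 1 candidate. The age-adjusted clinical severity scale is the nearer in wording, but the article does not say that it is the one meant.

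**5. What follows if the age-adjusted scale is meant.** Table 1 gives ages 5–18 for it and 2–18 for the MFM. Both ranges end at 18, so they differ only at the lower end. With age in whole years and follow-up at baseline age + 2:

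| Age at baseline | Age at 2 years | MFM available | Age-adjusted scale available |
|---|---|---|---|
| 0–1 | 2–3 | 2 years only | neither visit |
| 2 | 4 | both visits | neither visit |
| 3–4 | 5–6 | both visits | 2 years only |

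From a baseline age of 5 the lower limits no longer separate the two. A child aged 2–4 at a visit therefore has an MFM value but no modelled outcome at that visit. The article expects 20–30 children and gives no age distribution, so the number affected cannot be derived. If the FSHD evaluation score is meant, Table 1 gives no age limit and this step does not apply.

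**The case against.** The strongest defence is that primary outcome in the Statistics section means only the dependent variable of the mixed model. The position of the sentence supports this, the study calls itself explorative, its primary objective is descriptive, and progression is a secondary objective. No test or decision rule depends on which outcome is primary. On this reading the fault is a badly chosen label in a secondary analysis. The defence lowers the stakes, but the label still conflicts with three other places, and the MFM still has no stated longitudinal model. Nor is this detail that an article may leave to a fuller plan: it is a conflicting statement, and an author of such a plan could not tell which one governs.

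Several stronger readings are tempting, and the documents do not support them:

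- **The MFM is never analysed or modelled.** It is in the Spearman list and falls under the descriptive statistics. The regression outcome is disease severity with no instrument named, which does not rule it out.
- **The severity scales are collected only for validation.** The article gives validity as a purpose, not as the sole one, and a severity score also appears in the correlations and in the model.
- **An ordinal score is wrongly treated as continuous.** The article calls the score continuous, and its construction lies in cited sources that are not shown.
- **A fixed share of the cohort is lost.** Ages spread evenly over 0–17 would put 5/18 = 28% below the lower limit of the age-adjusted scale at baseline, against 2/18 = 11% for the MFM. This rests on a guessed instrument and an assumed age spread. In a cohort that must have symptoms, of a disease that typically begins in adolescence, the share under 5 may well be smaller. Some of these children also enter at follow-up.
- **The earliest-onset group is excluded.** This confuses current age with age at onset. Children with early onset who are now 5 or older remain in the model.
- **Age is counted twice.** This depends on which scale is meant and on how its adjustment works, which is not shown. Keeping age as a covariate beside an age-adjusted outcome is not in itself an error.
- **The primary outcome will be chosen after the results are known.** Two labels leave room for this, but nothing in the article shows such an intent, and three of the four places agree on the MFM.

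**Conclusion.** The point holds as a contradiction in the current text. The MFM is declared primary in three places. The Statistics section gives that label to the severity score and makes it the only outcome named for the 2-year mixed models. As written, the declared primary outcome has no stated longitudinal model, although it is measured at both visits and motor functioning is where the authors expect a 2-year difference. The instrument modelled in its place is not exactly identified, and either candidate is a secondary scale whose validity in children is under study.

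The size is that count: no stated longitudinal model for the MFM against one for the severity score. The further loss of modelled values at ages 2–4 is conditional on the age-adjusted scale being the one meant, and its extent cannot be given from the article. The conclusion assumes that the sentence on the primary outcome governs the mixed models, as its position between the model and the fixed effects indicates. If it does not, the mixed models have no named outcome at all, and the conflict over the label remains.

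**What to change.** In the Statistics section, name the MFM as the primary outcome and as the dependent variable of the linear mixed model for the 2-year data. Keep the severity-score model as a secondary analysis, and give the scale its exact Table 1 name so that it is clear which instrument, and which age range, is meant.

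If the severity score is truly intended as primary, leave the Statistics section's choice in place, change the abstract, Table 1 and the outcome text to match, and give the reason.

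The cost is a change of wording and one additional model. Both instruments are already scheduled at both visits, so no new data are needed. The change should be made before the follow-up data are analysed.

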## Objectives

The primary objective of the study is:to assess the clinical, genetic and epigenetic features of children with FSHD to optimize clinical management.The secondary objectives are:to define a new comprehensive definition of early onset FSHD;to provide prevalence estimations of early onset FSHD in The Netherlands;to establish a well-characterized baseline cohort for prospective follow-up and recruitment for future clinical trials;to assess 2-year disease progression rate in children with FSHD and develop a prognostic model.

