### Assessments

Participants will be invited for a baseline visit at the department of paediatric neurology at the Radboud University Medical Center. If the patient is unable to visit the hospital, the patient is offered a home visit and auditory, ophthalmologic and ultrasonography procedures will be omitted. Patients will have a follow-up visit after 2 years.

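### The mixed model for the 2-year data has no time term other than an undefined 'current age', so it either blends cross-sectional and within-child ageing or cannot estimate progression at all

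*Protocol article*

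**What the plan says.** One secondary objective is "to assess 2-year disease progression rate in children with FSHD and develop a prognostic model" (Objectives). The Statistics section states that "for the 2 year follow-up data, linear mixed models will be applied for analysis of differences in disease progression". It names the outcome ("The primary outcome is a continuous variable, FSHD clinical severity score") and then lists the model terms: "The fixed effect predictors are repeat length (divided in 1–3 D4Z4 repeat units (U), 4–6 U and 7–10 U"), followed by "current age, hereditary pattern and sex".

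The list has no visit, time-since-baseline or baseline-age term. Random effects are not described, and the article does not say whether 'current age' is age at each visit or age at entry. Each child has two assessments: a baseline visit, and then "Patients will have a follow-up visit after 2 years" (Assessments). On who enters: "Eligible patients are children aged 0–17 years with symptoms of facioscapulohumeral dystrophy" (Study population).

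**The concern.** A progression rate is a change within the same child. In this model the only term that could carry such change is age, and age varies far more between children (up to 17 years at entry) than within a child (2 years). A single age coefficient cannot tell a child growing two years older from a comparison of older with younger children.

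The two need not agree here. Children enter only if symptomatic. The Background section links childhood onset with more severe progression, and the Genetics section links short repeats with earlier onset. The youngest participants may therefore be a severe selection, which would flatten the cross-sectional age slope relative to the true course in a child. The rate is meant to support counselling and trial readiness, so an understated rate, with an interval that looks more precise than it should, would matter for both uses.

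**Working it through.** **Inputs from the article.** Two visits 2 years apart; entry ages 0–17; age-adjusted clinical severity scale listed for ages 5–18 (Table 1); 20–30 children expected. The article states no progression rate, score SD or intraclass correlation, so there is no planned figure to reproduce.

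**Assumptions.** A random intercept per child; intraclass correlation ρ of 0.80, 0.90 and 0.95; several age spreads with between-child variance V.

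**Reading A: age at each visit.** Each child's two ages lie 1 year either side of that child's mean, so the within-child sum of squares is 1² + 1² = 2. With the score variance scaled to 1, the information per child is:

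- within child: 2/(1−ρ)
- between children: 2V/((1−ρ)+2ρ) = 2V/(1+ρ)

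The cross-sectional share of the single age coefficient is w = [V/(1+ρ)] / [V/(1+ρ) + 1/(1−ρ)].

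Example, ages uniform over 5–18 (V = 13²/12 = 14.1) and ρ = 0.90: 14.1/1.90 = 7.4; 1/0.10 = 10; w = 7.4/17.4 = 43%.

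| Assumed ages | V | ρ = 0.80 | ρ = 0.90 | ρ = 0.95 |
|---|---|---|---|---|
| uniform 5–16 | 10.1 | 53% | 35% | 21% |
| uniform 5–18 | 14.1 | 61% | 43% | 27% |
| SD 4.5 | 20.25 | 69% | 52% | 34% |
| uniform 0–18 | 27.0 | 75% | 59% | 41% |

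The share falls below one half once ρ exceeds (V−1)/(V+1): 13.1/15.1 = 0.87 for ages 5–18 and 26/28 = 0.93 for ages 0–18.

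**Bias.** The coefficient estimates w × (between-child slope) + (1−w) × (within-child slope), so the bias is w × (between − within). A simulation with 25 children, entry ages uniform 5–16, a true within-child slope of 0.20 per year and 300 runs per setting agrees with this:

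| Cross-sectional slope | ρ = 0.80: formula / simulated | ρ = 0.90 | ρ = 0.95 |
|---|---|---|---|
| 0.20 (equal) | 0.200 / 0.201 | 0.200 / 0.200 | 0.200 / 0.199 |
| 0.10 | 0.147 / 0.147 | 0.165 / 0.169 | 0.179 / 0.181 |
| 0 (extreme) | 0.094 / 0.097 | 0.131 / 0.137 | 0.159 / 0.168 |

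With baseline age and years since baseline as separate terms, the simulated rate averaged 0.197 to 0.206 in every setting.

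In the extreme case of a flat cross-sectional slope, with a true rate of 0.15 SD per year and 600 runs, the 95% interval from the single-age model covered the truth in 58%, 70% and 82% of runs at the three values of ρ. The split model covered it in 94–95%.

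**Reading B: age at baseline.** Every fixed effect then has the same value at both visits, so the fitted mean is the same at both visits. No parameter represents change, and no rate can be read from the model.

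**The case against.** *The size and the bias are not established.* This stands. A reader might infer that the estimate is mainly cross-sectional and therefore biased. The documents do not support that: ρ and the age spread are not given, the cross-sectional part is the smaller one when ρ is high, and there is no bias if the two slopes are equal. A flat cross-sectional slope is an extreme case with no source in the article.

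*Repeat length is already in the model.* This stands in part. It absorbs some of the selection through short repeats. However, the Classification and Genetics sections themselves describe the link between repeat length and severity as inconsistent and imperfect, so some selection can remain. In one illustrative simulation with selection by onset and repeat class in the model (the strength of selection was invented), the single-age model averaged 0.128, 0.135 and 0.144 against a true 0.15 at ρ of 0.80, 0.90 and 0.95. Coverage was 90–93%. The bias was small but still downward.

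*The plan does not say that the age coefficient is the progression rate.* Correct. Descriptive statistics could report the raw 2-year change, so it would go too far to say that the plan will report little or no progression. But this is the only inferential model given for the follow-up data.

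*The outcome is not pinned down.* The severity score named in Statistics matches neither severity measure in Table 1 word for word. If the age-adjusted scale is meant, a linear decline is only a rough picture. That affects the magnitudes, not the missing time term.

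*A condensed article may leave time coding to a fuller plan.* Random effects and covariance structure, yes. The fixed effects, however, are enumerated as the model's terms, and the list as given does not serve the objective.

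**Conclusion.** The point holds in conditional form. As written, the model has no explicit time term, and its one age term fails on either reading. As age at each visit, the estimate mixes cross-sectional and within-child slopes, with a cross-sectional share of roughly 20% to 75%. As age at baseline, the model estimates no progression. The share rests on an assumed random intercept, ρ between 0.80 and 0.95, and age variances from 10.1 to 27.0. Bias requires the two slopes to differ. The article gives reasons to expect this, probably towards understating progression, but does not show it. The study is exploratory and the rate is a secondary objective, so this is a correction that should be made and not a threat to the study as a whole.

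**What to change.** In the Statistics section, replace 'current age' in the mixed model with two terms: age at baseline and years since baseline. Report the years-since-baseline coefficient with its 95% interval as the average progression rate, and present the baseline-age coefficient as a cross-sectional difference only. This settles both readings of 'current age'.

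No new data are needed. The cost is one extra degree of freedom and a wider interval, because the rate no longer borrows from differences between children. The standard error grows by a factor of 1/√(1−w). For ages 5–16 that is 1/√0.47 = 1.46 at ρ = 0.80, 1/√0.65 = 1.24 at 0.90 and 1/√0.79 = 1.12 at 0.95.

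Whether predictors should interact with time, to address differences in progression, is a separate question. It cannot be taken up until the model has a time variable.
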